## Abstract

**Background:**

First-episode psychosis most often has its onset during late adolescence. In caring for the young person, families endure high levels of stress and depression. Meanwhile, the social networks of families often erode. Our group has previously shown that family cognitive behaviour therapy (CBT) leads to significantly improved perceived stress compared with specialist first-episode treatment as usual; however, there are well-known barriers to the dissemination of effective family interventions. To address this, we have developed a novel online intervention entitled ‘Altitudes’ that fully integrates purpose-built online social networking, expert and peer moderation, and evidence-based psychoeducation within a single application. The primary aim of this trial is to evaluate the effectiveness of Altitudes in reducing stress in carers over a 6-month period.

**Methods/design:**

We describe here a single-blinded cluster randomised controlled trial (cRCT) with permutated blocks. The clusters comprise individual families. The two treatment conditions include Altitudes plus Specialist Treatment as Usual (STAU) and STAU alone. Altitudes involves participation in our novel online programme whereas STAU comprises specialist family work at the Early Psychosis Prevention and Intervention Centre (EPPIC), Melbourne, Australia. We aim to recruit 160 family members of young, 15–27 year-old, patients registered for treatment for first-episode psychosis (FEP) at EPPIC. The design includes two assessment time points, namely, baseline and 6-month follow-up. The study is due for completion within 2 years including an 18-month recruitment period and a 6-month treatment phase. The primary outcome is carers’ perceived stress at 6 months. Secondary outcome measures include a biomarker of stress, depressive symptoms, worry, substance use, loneliness, social support, satisfaction with life, and a range of measures that tap into coping resources. We seek to gain a dynamic picture of carer stress through our Smartphone Ecological Momentary Assessment (SEMA) tool.

**Discussion:**

This is the first randomised controlled trial designed to evaluate an online intervention for carers of young people recovering from FEP. It has the potential to produce evidence in support of a highly novel, accessible, and cost-effective intervention to reduce stress in carers who are providing support to young people at a critical phase in their recovery from psychosis.

**Trial registration:**

Australian New Zealand Clinical Trial Registry, identifier: ACTRN12616000968471. Retrospectively registered on 22 July 2016.

**Electronic supplementary material:**

The online version of this article (doi:10.1186/s13063-016-1775-5) contains supplementary material, which is available to authorized users.

## Background

Psychosis is a severe mental disorder, which impacts not only the individual but also their family. Family members caring for a relative with psychosis often suffer significant levels of distress [1]. Fortunately, the acute symptoms of psychosis, which most often have their onset in late adolescence, typically respond to treatment [2]. However, full recovery of functioning is a longer-term process taking several years in many cases [3]. Young people recovering from first-episode psychosis (FEP) typically face elevated risks of depression [4], social anxiety [5], substance abuse [6], and long-term challenges in returning to meaningful activities [7]. Forty percent of first-episode patients suffer psychotic relapse over the first 2 years after treatment is commenced [8].

### The experience of caregiving

Family members caring for the young person with FEP also suffer from a range of significant physical and mental health problems. Investigations into the experience of caring for a relative have revealed that throughout the early stages of psychosis, family members have a significant involvement in a young person’s life; 80–90% of young FEP service consumers reside in the family home [9]. The commencement of acute-phase treatment for psychosis is often overwhelming for families and has been compared to bereavement [10]. During this period family members face the risk of exposure to traumas, such as violence perpetrated by the young person [11, 12], and families worry frequently about behavioural changes [13]. Twenty-six per cent of FEP family carers experience severe stress and a similar proportion suffer from moderate stress [14]. Depression is also common among family carers, with one third suffering clear depressive symptoms and another third mild depression [15]. Meanwhile, the burden of the caring role has been shown to significantly deplete family social networks, an important buffer for stress [16]. Although less is known about the physical health correlates of caring for a relative with psychosis, there is evidence that the style of caring and severity of psychotic symptoms increases the risk of physical health problems for relatives [17, 18]. Findings from investigations of Alzheimer’s disease provide a basis for further hypotheses – studies have suggested that stress is associated with weakening of carers’ immune functioning and accelerated ageing [19].

### Carers’ appraisals and the course of psychosis

We previously demonstrated that positive reappraisals by carers promote carer coping and reduced distress [20]. Carers’ appraisals of their relative’s disorder are also known to influence their communication with their relative. For example, if family members blame themselves for the psychosis they are significantly more likely to become emotionally over-involved with their relative [15]; we have shown that emotional over-involvement predicts burden of care and stress levels in families [21]. These are doubly important processes because these family communication patterns influence the course of psychosis – in particular, criticism and emotional over-involvement significantly increase the risks of psychotic relapse [22]. Therefore, for the mental health of all family members, it is critical to identify effective ways of reducing carers’ stress by encouraging positive reappraisal and by increasing the capacity of the family to respond adaptively to the young person affected by psychosis.

### The evidence for the effectiveness of family interventions for psychosis

Meta-analyses of randomised controlled trials (RCTs) of carer interventions in chronic psychosis have shown robust beneficial treatment effects leading to reduced rates of relapse in patients diagnosed with psychosis [23]. There is emerging evidence that carers also directly benefit from targeted interventions [24] and such interventions have been proven to be cost-effective [25]. These treatments are typically based upon cognitive behaviour therapy (CBT) with a focus on psychoeducation and training in structured problem solving and communication skills. Family interventions have also been structured to cater for multiple families simultaneously (i.e. multifamily therapy) with the added component of encouraging support between families [26].

Correctly targeted family intervention in the early stages after FEP may alter the long-term trajectory of family stress [27] and may improve the long-term outcomes for the young person [28]. The evidence base for the effectiveness of family interventions in FEP, however, is less well developed than for chronic psychosis [9].

Our group has published one of the few RCTs designed to evaluate an intervention specifically developed for FEP families whose relatives were receiving treatment at the Early Psychosis Prevention and Intervention Centre (EPPIC), a formative specialist FEP service in Melbourne, Australia [27]. In one treatment arm of the 30-month follow-up study, families and their young relative diagnosed with FEP received parallel CBT. This package of interventions, provided over a 7-month period, was compared with ‘gold-standard’ specialist treatment as usual (STAU) within a FEP service, and not generic ‘usual care’. Perceived stress related to caregiving was significantly improved in the family CBT condition compared to STAU at 30 months’ follow-up. In a separate study conducted at EPPIC, McCann and colleagues showed that FEP families randomised to self-guided bibliotherapy, a treatment based on problem-solving therapy, showed more favourable outcomes on positive caregiving experiences compared with those receiving STAU at 16 weeks’ follow-up [29].

Despite these promising results, a major gulf remains between the efficacy and the availability of family treatments in FEP. This gap is most evident for regular interventions or supportive structures for the families of all FEP patients, as well as being a concern for more complex cases where expert support is needed [30–32]. Evidence-based interventions are perceived as costly with the result that most families do not receive them. Where family interventions are available they are typically focussed upon the prevention of relapse and not on the wellbeing of the family members.

In this context the Internet may prove an important cost-effective and accessible resource for both online social support and for the provision of expert evidence-based interventions. The social isolation and vicarious stigma experienced by families, and the high value placed on opportunities to share concerns and effectively solve problems with other families [33], suggest that safe and structured online social networking may provide benefits. Online social networking offers the promise of high cost-effectiveness, wide dissemination, optimal engagement, and high accessibility that extends well beyond the limitations of the clinic setting.

Despite these possibilities we are aware of only two published studies in the psychosis field that have utilised information communication technology for carers, which involved variations of social networking [34, 35]. Neither study was designed specifically for FEP carers, and only one was an RCT [35]. In brief, these studies have demonstrated the acceptability of online interventions for carers of individuals with schizophrenia but have not provided specific evidence for the efficacy of online intervention for FEP carers.

We have successfully developed and piloted a new carer intervention entitled ‘Altitudes’ for carers with a young relative recovering from psychosis, after previously piloting the system with carers of young people with depression and anxiety. Altitudes integrates purpose-built online social networking, expert and peer moderation, and evidence-based psychoeducation within a single application. Altitudes was developed using participatory design principles in consultation with carers and with family peer-support staff members at Orygen Youth Health (OYH).

Altitudes is one of several applications derived from our Moderated Online Social Therapy (MOST) software framework. MOST was developed with a multidisciplinary team of clinical psychologists, psychiatrists, web designers, computer programmers and professional writers. Other examples of MOST applications include ‘Horyzons’ which was built specifically for service consumers with early psychosis [36].

We believe that Altitudes provides a unique opportunity to extend the availability of evidence-based family intervention for FEP families. Here, we describe the protocol for the Altitudes trial.

### Aims and hypotheses

The overall aim of this trial is to determine the effectiveness and cost-effectiveness of Altitudes for carers’ of young people with FEP. The primary hypothesis is that Altitudes plus specialist first-episode family treatment as usual (STAU), compared with STAU alone, will be superior in relation to carers’ perceived stress at 6 months’ follow-up. STAU was selected to test whether Altitudes affords improved outcomes in comparison with current best practice in FEP. Second, we hypothesise that Altitudes plus STAU will be superior to STAU at 6 months’ follow-up in relation to an objective measure of stress, carers’ depression, carers’ self-efficacy, and carers’ perceived social support.

A supplementary aim of the study is to understand the mechanisms underpinning stress in carers. A major innovation of this trial is the successful creation of a cutting edge Smartphone Ecological Momentary Assessment (SEMA) application. Using this technology, we aim to investigate how variance in carers’ stress and depression over time is accounted for by: (1) the nature of specific interactions with their young relative, (2) the content and level of conviction associated with specific appraisals of their relative’s behaviour, (3) the appraisal of emotional and social support from others, (4) specific coping responses to the young person’s behaviour, and (5) their perceived self-efficacy in caring for their young relative. Importantly, SEMA allows us to measure these potential mechanisms of therapeutic change in real time as they naturally occur in carers’ daily lives.

## Methods/design

### Study design

A cluster randomised controlled trial (cRCT), with families comprising clusters, is designed to test the effectiveness of Altitudes plus STAU (based upon our MOST software) compared with currently available STAU in improving stress at 6 months in carers of young people recovering from FEP.

The design includes two assessment time points, namely, baseline and 6 months’ follow-up with assessors kept blind at each time point. An additional interim interview is completed via telephone at approximately 3 months after the baseline assessment to assess perceived stress.

This cRCT includes an 18-month recruitment period and a 6-month treatment phase. The study will be completed within 2 years. The protocol’s development was guided by the Standard Protocol Items: Recommendations for Interventional Trials (SPIRIT) (Additional file 1) [37] and Good Clinical Practice guidelines [38].

### Setting

Recruitment of the trial participants commenced in October 2015 at EPPIC, a subprogramme of Orygen Youth Health (OYH). EPPIC is a specialist FEP programme that provides services to 250 new FEP patients per year [39]. EPPIC provides 18 months to 2 years of specialised care after which patients are discharged and transferred to standard treatment if required [40].

### Enrolment and randomisation

The recruitment and allocation is depicted in the flow diagram in Fig. 1. The study research assistants (RAs) regularly attend EPPIC clinical team meetings to promote the study. After the RA obtains written informed consent from each family member, families are randomised to Altitudes plus STAU or to STAU alone at a ratio of 1:1. We expect that participant numbers within clusters (i.e. families) are likely to vary from between one and four with a mean cluster size estimate of 1.3. An independent statistician created the randomisation sequence, which includes permutated blocks. The block sizes and randomisation sequence are concealed from the study RAs and investigators. Randomisation occurs after each baseline assessment. When a family member from a newly recruited family provides informed consent and completes the baseline assessment, the study coordinator randomises the family via a secure online Clinical Trials Management System (CTMS). The CTMS sends an automated email to the study coordinator and investigators notifying them of the outcome of randomisation. The study coordinator informs the family of the allocation.

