**Fig. 1 Fig1:**
[figure not shown]
Study flow diagram for Altitudes

The study RAs undertaking the follow-up assessments are kept blind to treatment allocation via the following mechanisms: (1) regular reminders are sent to all clinical staff at EPPIC regarding the importance of the blind, (2) at the commencement of each research interview the RA reminds participants of the importance of the blind, (3) study RAs are excluded from all clinically related discussions regarding participants, and (4) the RAs are forbidden from accessing participants’ medical records. The RAs record their best guess of participants’ treatment allocation at 6 months’ follow-up in order to enable an assessment of the success of treatment concealment.

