### Data integrity

A custom-built Clinical Trials Management System (CTMS) is used to manage the electronic data of this study. The CTMS includes an electronic Case Report Form (eCRF) and randomisation functionality. The study RAs record participant-level data on a paper-based Case Report Form (CRF). These data are subsequently entered into the eCRF section of the CTMS. The randomisation functionality of the CTMS is used to carry out the randomisation aspect of the study and is operated by the study coordinator. The CTMS is accessed using a secure website and is stored on a secure server. It is designed to maintain the privacy and confidentiality of participant information and to ensure the integrity of the data. Access to CTMS is restricted to study personnel and the level of access is dependent on the person’s role. In particular, the RAs and the investigators do not have access to the randomisation section of the CTMS to ensure that they remain blind. Data are accumulated on three separate secure computer servers, including data collected from the SEMA tool, CTMS and data accumulated from participant activity within the Altitudes online system. Data are also provided from the laboratory analysis of hair samples at the Stratech Scientific APAC laboratory. These various data are aggregated into a single electronic secure databank.

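### The trial system emails each family's allocation to the investigators, although the protocol limits their access to that system so that they stay blind

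*Protocol article*

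**What the plan says.** Two sections of the protocol article describe what the investigators may know.

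- **Enrolment and randomisation.** The study coordinator randomises a family through the Clinical Trials Management System (CTMS) once a member has consented and completed the baseline assessment. Then: "The CTMS sends an automated email to the study coordinator and investigators notifying them of the outcome of randomisation". The same section says: "The block sizes and randomisation sequence are concealed from the study RAs and investigators".
- **Data integrity.** The randomisation function of the CTMS "is operated by the study coordinator". Access depends on role, and "the RAs and the investigators do not have access to the randomisation section of the CTMS to ensure that they remain blind".

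Three other statements set the context. The abstract calls the trial a "single-blinded cluster randomised controlled trial (cRCT) with permutated blocks". The paragraph after Fig. 1 covers the RAs: "The study RAs undertaking the follow-up assessments are kept blind to treatment allocation via the following mechanisms". It lists four measures, all concerning the RAs, and adds a record of their guesses at allocation at 6 months.

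**The concern.** The data integrity section does more than describe user permissions. It gives the purpose of the restriction, which is that investigators remain blind. The enrolment section has the same system deliver to them what the restriction is meant to withhold.

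A safeguard that the protocol claims would therefore not exist in practice. The claim has some weight here because, as the Interventions section states, the trial team designed and built Altitudes, and the Discussion expects it to prove superior. A later report that relied on the data integrity text to say that investigators were blind would be contradicted by the trial's own published procedure.

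A second, smaller issue follows. Allocation is 1:1 in permuted blocks, and block sizes and sequence are to be hidden from investigators. A person who receives each outcome as it occurs sees the realised part of that sequence build up.

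**Working it through.** The plan gives no figure to reproduce on this point. The check is a comparison of text.

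**Step 1: who is meant to be blind.** Data integrity names two groups, RAs and investigators, and gives blindness as the reason for restricting both.

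**Step 2: who is told.** Enrolment and randomisation names two recipients of the automatic email, the study coordinator and the investigators.

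**Step 3: overlap.**

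| Role | Declared blind (Data integrity) | Sent the allocation (Enrolment and randomisation) |
|---|---|---|
| Study coordinator | No; operates randomisation | Yes |
| Investigators | Yes | Yes |
| RAs | Yes | No |

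Only the investigators' row conflicts. The coordinator's and RAs' rows are consistent.

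**Step 4: can both sentences be true?** Read literally, the restriction concerns a part of the CTMS and not knowledge of allocation, so an investigator could lack access and still get the email. But the stated purpose would then fail. Either the email is not sent to investigators as written, or they are not blind.

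**Step 5: does the single-blind label resolve it?** No. Blind assessors alone could satisfy that label, but the claim that investigators remain blind is made separately and would still be untrue.

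**Step 6: the block sequence.** In a 1:1 permuted block, once one arm has filled its half of the block, the remaining places are determined. A recipient who keeps the emails could come to infer the block structure and sometimes anticipate a later allocation. The block sizes are not given, so how often cannot be calculated.

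**Step 7: how many notifications.** Families are the unit of randomisation. Assuming the planned mean cluster size of 1.3 holds:

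- planned: 160 / 1.3 ≈ 123 families;
- randomised by September 2016: 75 / 1.3 ≈ 58 families;
- still to come: (160 − 75) / 1.3 = 85 / 1.3 ≈ 65 families.

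These are headcounts of notifications and do not measure bias.

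**The case against.** The best defence is that the blinding that bears most directly on outcome collection is intact. The trial is declared single-blind, the Study design section speaks of blind assessors, and the RAs have their own protective measures and are not emailed. All of this stands. A reader might infer that outcome assessment is unblinded, or that the only protection against bias has gone; the protocol supports neither. Nor would stopping the email blind the primary outcome: the Perceived Stress Scale is answered by carers, whom the coordinator tells their allocation.

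A reader might also see a matching conflict for the RAs: "The study research assistants (RAs) regularly attend EPPIC clinical team meetings to promote the study", yet "study RAs are excluded from all clinically related discussions regarding participants". The two are compatible. The stated reason for attending is to promote the study, and nothing says that the RAs stay while enrolled families are discussed.

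A third tempting inference is selection bias through predictable blocks. No route to it is described. The RAs obtain consent, the coordinator randomises after baseline, and investigators are given no part in enrolling families. The coordinator must see each allocation in any case, so changing the mailing list does not alter that. What remains is narrower: the emails sit badly with the statement that the sequence is concealed from investigators.

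The protocol also does not say that investigators supervise the RAs or take data decisions, so harm by that path would be an assumption. It does not say which investigators receive the email, or which of the two sentences is the mistake; a correction to the data integrity text alone would remove the inconsistency. None of this makes the two sentences agree.

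**Conclusion.** The point holds as an internal contradiction: investigators are declared blind in one section and sent each randomisation outcome in another, so the investigator blind does not exist as written. The emails also reveal to them the realised allocations of a list whose sequence is stated to be concealed from them.

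Its reach is each family randomised under this procedure, about 123 if recruitment reaches 160 carers at 1.3 per family. Its effect on the treatment estimate is unknown and cannot be derived from the protocol. The conclusion rests on reading the email sentence as current practice and the recipients as the same investigators whose access is restricted. It does not extend to the RAs' blinding, to the conduct of enrolment, or to any demonstrated bias in the primary outcome.

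**What to change.** 1. Take investigators off the automatic notification and send it to the study coordinator alone. The coordinator already randomises, informs families and inducts Altitudes users, and the protocol states no operational need for wider circulation. This restores the stated safeguard for families not yet randomised, about 65 by the count above.
2. If some investigators must know allocations, name them by role as unblinded, keep them out of assessment and analysis decisions, and correct the data integrity section so that it no longer describes them as blind.
3. For families already randomised, covering 75 participants by September 2016, record which investigators received allocations and report them as unblinded. Changing the mailing list cannot undo those disclosures.

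The cost is a change to a mailing list, one or two protocol sentences and a short log of past recipients. It needs no extra staff and no change to sample size or schedule.
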